## Methods: participants, interventions and outcomes

### Study setting {9}

Four UK research sites will take part in the trial: Institute of Psychiatry, Psychology & Neuroscience (KCL), University of Manchester, University of Glasgow and University College London. At least two local NHS sites will be attached to each of these research sites and therapy will take place in community settings.

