### Eligibility criteria {10}

The inclusion criteria for the study are as follows: (1) aged 18 years or over; (2) currently under the care of a specialist mental health team (inpatient and outpatient settings); (3) have current frequent and distressing voices, (as measured by a score of at least 1 on each of the intensity of distress and frequency items of the PSYRATS (Voices) scale), persisting for at least 6 months and spoken in English; (4) speak and read English to a sufficient level to provide consent and complete the assessment procedures; and (5) a clinical diagnosis of Schizophrenia spectrum disorder (ICD10 F20–29) or affective disorder with psychotic symptoms (ICD-10 F30–39, subcategories with psychotic symptoms) as determined through clinical records and additional consultation with the clinical team if unclear. Criteria for exclusion are as follows: (1) primary diagnosis of substance disorder, personality disorder or learning disability; (2) lacking capacity to consent; (3) profound visual/hearing impairment or insufficient comprehension of English to be able to engage in assessment or therapy; (4) currently undertaking individual psychological therapy for voices; and (5) currently experiencing an acute mental health crisis.

Therapy will be delivered by mental health clinicians, mostly psychologists, with experience of delivering psychological therapy to people with psychosis.

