#### Adverse event reporting and harms {22}

The occurrence of adverse events (AEs) will be monitored actively and systematically, following guidance from the Consolidated Standards of Reporting Trials (CONSORT) with the extension for social and psychological interventions, and the extension for reporting of harms. Medical Research Council Guidelines for Good Practice in Clinical Trials will also be followed to ensure good governance of the trial for integrity and participants’ safety and wellbeing.

AEs are defined as any untoward medical occurrence, unintended disease or injury, or untoward clinical signs in service user/patient participants, whether or not related to the therapy or device which require additional support or input from health professionals.

Adverse events will be initially assessed at three levels of intensity: mild, moderate and severe, which reflect the impact of the event on the person at the time. Please note there is a distinction between ‘severe’ and ‘serious’. Seriousness is the criteria for defining regulatory reporting obligations and the following will be considered as serious adverse events (SAE, categories A–C): All deaths (category A), incidents which acutely jeopardise the health or psychological wellbeing of the individual, resulting in immediate hospital admission and/or permanent disability (category B), or resulting in injury requiring immediate medical attention (category C). These SAEs will include but are not limited to (1) hospital admissions; (2) home treatment team involvement; (3) suicide attempts; (4) any violent incident necessitating police involvement (whether victim or accused); (5) self-harming behaviour; and (6) all deaths. In order to ensure active surveillance of harms, at each assessment point, research workers will utilise the interview to actively check for the occurrence of specific AEs. At the completion of the trial, all medical notes will be checked, for the total duration of enrolment, for any previously undisclosed record of AEs. Reasons for withdrawal from the study will also be recorded.

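### Inpatients are eligible, but the SAE definition has no criterion for worsening in a participant who is already in hospital

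*Protocol article*

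**What the plan says.** Eligibility criteria {10} takes in people "currently under the care of a specialist mental health team (inpatient and outpatient settings"). It excludes anyone "currently experiencing an acute mental health crisis", but being an inpatient is not itself an exclusion.

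Adverse event reporting and harms {22} defines an SAE by three lettered categories:

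- A: any death.
- B: "incidents which acutely jeopardise the health or psychological wellbeing of the individual, resulting in immediate hospital admission and/or permanent disability (category B").
- C: such an incident "or resulting in injury requiring immediate medical attention (category C").

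An illustrative list follows: "These SAEs will include but are not limited to (1) hospital admissions; (2) home treatment team involvement; (3) suicide attempts". It continues with "any violent incident necessitating police involvement (whether victim or accused"), self-harming behaviour and deaths. The same section separates severity from seriousness, and says that seriousness sets the regulatory reporting obligations. SAEs go immediately to the Chief Investigator, the site Principal Investigator and the DMEC chair. Other adverse events are reviewed at DMEC meetings or whenever the chair asks.

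**The concern.** Hospital admission is the main route by which a purely psychiatric relapse becomes serious under this definition. That route works for someone living in the community, but someone already on a ward cannot ordinarily be admitted again. Nothing in the definition takes its place, such as a lengthened stay. Applied as written, the rule can therefore class the same clinical event differently according to where the participant happens to be.

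This matters because psychological worsening is a harm the trial particularly needs to detect. The Background describes the avatar delivering the voice's own threats and abuse, and the Discussion calls the early sessions anxiety-provoking. Criteria for discontinuing or modifying allocated interventions {11b} foresees therapy being stopped for marked worsening of mental health. There it asks only for an adverse event form, so whether that event is also an SAE depends entirely on the definition in {22}. At stake is prompt notice to the people responsible for safety oversight.

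**Working it through.** No arithmetic applies, because the point rests on wording. The check takes each stated route to SAE status and asks whether it is open to an outpatient and to a participant already in hospital.

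| Route in {22} | Outpatient | Current inpatient |
|---|---|---|
| Death (A) | open | open |
| Immediate hospital admission (B, list item 1) | open | not ordinarily; perhaps on transfer to another hospital |
| Permanent disability (B) | open | open |
| Injury needing immediate attention (C) | open | open |
| Home treatment team involvement (list item 2) | open | not while on the ward; possible on discharge |
| Suicide attempt (list item 3) | open | open |
| Violence with police involvement (list item 4) | open | open |
| Self-harm (list item 5) | open | open |

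Now take an acute psychiatric deterioration with none of the features that are open in both columns.

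1. In an outpatient it leads to admission or to home treatment team involvement, and either makes it an SAE.
2. In an inpatient, suppose its only consequence is a longer stay. It then meets no lettered category and no listed example.
3. Grading it severe does not help, because {22} says that severe and serious are different things.
4. The open wording of the list does not clearly help either. The list begins by referring back to the SAEs just defined, so it reads as illustrating A to C and not as adding a further outcome.
5. The event therefore falls back to adverse event status, which requires only that extra support or input from health professionals was needed.

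The group concerned is not limited to people who are inpatients at entry. Someone admitted during the 28 weeks has an SAE at the admission, but later worsening within that stay has the same unclear status.

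The consequence follows from the reporting sections. Without SAE status there is no immediate notification under {22}. Three slower routes remain:

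- Monthly site reports on adverse events go to the trial management committee, which the Chief Investigator chairs (Composition of the coordinating centre and trial steering committee {5d}).
- The DMEC receives regular adverse event reports and meets at least annually (Composition of the data monitoring committee {21a}).
- The DMEC chair can ask for a full adverse event report at any time ({22}).

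**The case against.** The strongest reply is that the definition is wider than admission. Category B has permanent disability as an alternative, category C needs only an injury, and suicide attempts, self-harm and police-involved violence are listed separately. This is correct. A reader might infer that nothing happening to an inpatient counts as serious without a new admission, and the article does not support that.

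A second reply is that the list is expressly open and already goes beyond a literal reading of B and C, since home treatment team involvement need not end in admission, disability or injury. An assessor could therefore class a grave inpatient deterioration as serious. This stands in part: the right description is *not clearly serious*, not *excluded*. It does not remove the gap, because the outcome then depends on individual judgement with no stated criterion.

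Third, the event is still captured. Adverse events are actively checked at each assessment, medical notes are searched at the end, and the reporting routes above apply. This also stands. A reader might infer that the DMEC would learn of such an event only at an annual meeting, and the text contradicts that.

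Fourth, the affected group may be small. The exclusion for acute crisis probably removes some inpatients at entry, and the gap applies only to days spent in hospital. That is fair, and the article gives no count.

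Fifth, an article condenses a fuller protocol that may contain seriousness guidance. That would excuse a missing detail. Here, however, the article sets out the definition in full, with categories and examples, and as stated it does not fit the population it recruits.

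**Conclusion.** The point holds in a limited form. The SAE definition has no criterion for a prolonged stay or equivalent worsening in a participant already in hospital. Psychiatric deterioration without any of the other listed features is then not clearly serious in an inpatient, although it would be in an outpatient. The practical loss is immediate notification; recording and routine review remain.

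The size cannot be given. The article states neither the inpatient share nor the expected number of admissions, and any percentage would be a guess. The conclusion assumes that the list illustrates categories A to C and that no fuller seriousness guidance exists elsewhere.

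Two further inferences should be resisted. One is that SAE rates are biased between arms because care setting is not a stratification factor: randomisation balances setting in expectation, so only chance imbalance remains. The other is that Study setting {9} contradicts the eligibility criteria by saying that "therapy will take place in community settings". That sentence concerns where therapy is delivered, and the criterion concerns which services a participant may be under. It does not show that the definition was written with outpatients alone in mind.

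**What to change.** Reconcile Eligibility criteria {10} with Adverse event reporting and harms {22} by adding to category B a reporting criterion for participants already in hospital, for example *or prolongation of an existing admission*. State that it also applies to participants admitted during the trial. Add one field to the adverse event form for care setting at event onset, so that events in hospital can be identified when SAEs are summarised.

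This changes a reporting definition only and leaves clinical care as it is. It costs one clause and one form field, with a slightly higher SAE count to report and review.

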##### COVID-19

In addition to our recording of adverse events as described above, we will add a category for identification of adverse events as remote-delivery-related. This will ensure we capture any adverse events that may be specifically related to the delivery of assessments or therapy remotely.

#### Frequency and plans for auditing trial conduct {23}

The roles of the TSC and the DMEC are to ensure the trial is conducted to a high standard; these committees are independent from the investigators and sponsor. The DMEC will receive open reports showing summary measures of the data across the sample and will be the only committee to receive closed reports displaying summary measures of the data split by treatment group.

#### Plans for communicating important protocol amendments to relevant parties (e.g. trial participants, ethical committees) {25}

Any important protocol amendments will be submitted for approval to the research ethics committee and the Trial steering Committee for approval, subsequent changes will then be made and recorded in the trial protocol and the ISRTCN registration.

#### Dissemination plans {31a}

It is intended that the results of the study will be reported and disseminated at international conferences and in peer-reviewed scientific journals and will be made available to participants and clinical teams in an accessible format and on the study website. It will also be accessible in print and digital media and presented at stakeholder events. The trial is intended as an important step towards the dissemination of the therapy into routine care, if efficacy is established. If the success of earlier trials is replicated and we can demonstrate that it is feasible to train a larger workforce, next steps would include licensed provision of the AVATAR therapy software and training in therapy to interested parties both in the UK and elsewhere.

## Discussion

AVATAR therapy is a relational therapy for distressing voices involving direct dialogue with a digital representation of the main voice the person hears. Encouraging pilot work [15] led to a fully powered RCT in which AVATAR Therapy was found to be superior to an active control post-therapy with a large effect size of 0.8 [16]. Delivery of AVATAR Therapy in this recent trial resulted in an evolution in our understanding of the core therapy processes and how these might, in principle, differ between a standardised phase 1 focusing on exposure and assertiveness, and a formulation-driven phase 2 incorporating a broader range of treatment targets [14]. Data from the previous trial suggest that anxiety reduction is especially prominent during phase 1, but that other processes during phase 2, including changes in the perceived omnipotence and malevolence of the voice, may contribute to improved treatment outcomes, at least for some participants [17]. The new trial develops these insights and aims to make progress towards increased availability of AVATAR therapy in routine mental health care. In addition to testing efficacy of AVATAR-brief and AVATAR-extended, our examination of mediation will also provide understanding of the mechanisms of therapeutic change. The trial will also provide important information on whether, if the therapy is shown to be effective, this is influenced by the complexity of characterisation of the voice. Other clinical characteristics which might plausibly influence AVATAR treatment effectiveness (e.g. trauma experiences and negative symptoms) will be included in exploratory moderation analyses. In AVATAR2 we will harness the ecological validity of ESM to capture changes in anxiety and the relationship with the voice in daily life at each time-point. Finally, the incremental cost-effectiveness of both AVATAR-brief and AVATAR-extended compared to TAU will also inform future strategies for therapist training and wider provision.

The trial will also allow testing of the AVATAR software platform across multiple sites with participants and therapists recruited from several NHS settings serving both urban and rural populations. It is likely that a proportion of participants will be recruited, assessed and indeed receive therapy remotely. At the time of writing this protocol, the UK is experiencing a second surge in COVID-19 cases. As a result, many clinical services have reduced face-to-face contact for all but urgent purposes and a range of social distancing and other restrictions are periodically imposed in localities or UK nations. Recruitment strategies including meetings with clinicians will be carried out virtually, as required, as will procedures for obtaining consent and data capture. Previously, AVATAR therapy was delivered in clinic settings and although the therapist conducted the dialogue from a separate room, he/she was nevertheless available in person at any point during the therapy. Although remote delivery of therapy is now technically feasible, there are anticipated to be challenges in terms of recruitment and the practical feasibility of delivering sessions increasing the importance of careful monitoring of treatment adherence and fidelity. Whilst we have the technology to deliver therapy via a secure, encrypted system and we can supply the necessary hardware to participants, the extensive geography of the new trial may bring challenges of connectivity and other in-session technical difficulties. The fact that the therapist is not immediately on hand may also be a barrier to recruitment or continued participation especially in the anxiety-provoking early sessions and brief therapy. Communication with the participant’s usual clinical team may also be delayed. Given these potential challenges, detailed standard operating procedures for remote recruitment, assessment and therapy delivery have been developed, the latter informed by recent evidence of successful remote delivery of psychological therapy including trauma-focused work which shares AVATAR therapy’s approach to working in the context of high affect [51]. We anticipate the possibility of conducting sub-analyses that take account of whether data collection and/or therapy were delivered remotely and of the wider covid-19 context.

AVATAR therapy is multifaceted and therapy delivery requires skill, sensitivity, and effective training and supervision [14]. Therapists on the previous trial were four doctoral-level psychologists and one senior consultant psychiatrist, all experienced clinicians with prior expertise in working within a cognitive-behavioural therapy approach for psychosis. The majority of the therapy-specific interventions were developed and refined in the earlier trial. Whilst interest in the approach is growing; for example, with independent pilot work conducted by other research groups [52], the small number of therapists who have delivered AVATAR therapy as pioneered by [name] and developed within our team remains a significant barrier to wider dissemination. The present study extends training to approximately 20 clinicians across at least 8 NHS settings with planned assessments of fidelity and competence in delivering the therapy.

The findings of this trial will provide further data on efficacy and cost-effectiveness across multiple clinical settings, and lead to the optimisation and increased personalisation of the AVATAR therapy approach. This will pave the way, should the findings be positive, to wider therapy training and implementation in the future.

## Trial status

Protocol Version Number: 1.2, Date: 28/10/20.

Recruitment will begin in January 2021 and will be completed in November 2022 with the final follow-up data collected in March 2023.

## Data Availability

The datasets generated and/or analysed during the current study will be available in anonymised form, and the corresponding statistical code, from the research team on reasonable request, subject to review, following the publication of trial results. The Avatar Therapy software will be made available for licence at the end of the trial.

## Abbreviations

AE: Adverse event
AVH: Auditory verbal hallucinations
AVATAR: Audio Visual Assisted Therapy Aid for Refractory auditory hallucinations
BAVQ-R: Beliefs about Voices Questionnaire Revised version
BDI-II: Beck Depression Inventory–II
CAINS: Clinical Assessment Interview for Negative Symptoms
CBTp: Cognitive behavioural therapy for psychosis
CHOICE: The Choice of Outcome in CBT for Psychosis
CI: Chief Investigator
CONSORT: Consolidated Standards of Reporting Trials
CSRI: Clinical Service Receipt Inventory
CTU: Clinical Trials Unit
DASS-21: Depression Anxiety and Stress Scale
DMEC: Data Monitoring and Ethics Committee
EDC: Electronic data capture
ESM: Experience Sampling Methodology
GDPR: General Data Protection Regulation
NHS: National Health Service
ICD: International Classification of Diseases
ISRTCN: International Standard Registered Clinical/soCial sTudy Number
ITQ: International Trauma Questionnaire
KCL: King’s College London
PSYRATS: Psychotic Symptoms Rating Scale
PTSD: Post-traumatic stress disorder
QALY: Quality-adjusted life year
RCT: Randomised controlled trial
REDCap: Research Electronic Data Capture
RQ: Relationships Questionnaire
SAE: Serious adverse event
SAPS: Scale for Assessment of Positive Symptoms
SC: Supportive counselling
SCAN: Schedules for Clinical Assessment in Neuropsychiatry
Mini-TALE: Mini-Trauma and Life Events Checklist
TAU: Treatment as usual
TMC: Trial Management Committee
TVAQ: Trauma Voice Associations Questionnaire
TSC: Trial Steering Committee
VAAS: Voice Acceptance and Action Scale
VPDS: Voice Power Differential Scale
WAI: Working Alliance Inventory
WEMWBS: Warwick Edinburgh Mental Wellbeing Scale
WT: Welcome Trust
